**Table 1 Tab1:**
[figure not shown]
Trial Enrolment and Variables per Visit

### Data collection, data management, confidentiality and access to data

Data is collected from the electronic medical chart and the filled in questionnaire by patients. It is stored in a secure database, REDcap [17, 18]. All data stored will be stored anonymously. Patients will be identifiable through a unique code. This code will be stored at a secured server, only accessible by the principal investigator and one member of the research team collecting the data. The data will be stored for 15 years after the study has ended.

### Data monitoring, harms and auditing

A data monitoring committee will be provided for by the sponsor. They have no competing interest as the sponsor is a non-profit organization. No interim analyses will be performed. Serious Adverse Events and Adverse Events will be reported to the METC. Auditing will be performed by the METC.

### Sample size, recruitment and consent

Malay et al. identified a minimal clinically import change (MCIC) at 3, 6, and 12 months’ time-points of 0.4, 0.7, and 0.7 points on a 5-point scale for symptom severity score of the BCTQ questionnaire and 0.3, 0.3, and 0.4 points on a 5-point scale for function status scale [19]. The standard deviation used is 0.7, based on a 12 months follow-up after decompression [20].

Using a sample size formula for continuous outcomes in a longitudinal study, a total of 144 patients will be needed (α = 0.05, β = 0.80). Taking into account a dropout of 10%, we will include 160 patients.

Patients will be identified and invited for the study at the neurological outpatient clinic. Study information will be given and time to overthink participation. During the first outpatient clinic visit at the plastic surgery department, patients will get the chance to ask questions and sign written informed consent with the surgeon or resident present.

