### Outcomes

#### Primary outcome

The difference in change (Δ, preoperatively and postoperatively) in BCTQ score between both treatment groups at 3, 6 and 12 and 18 months follow-up.

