### Statistical methods

#### Primary study parameter

Difference in change in BCTQ: Linear generalized estimating equation (GEE) analyses will be used to study the longitudinal relationship between treatment group (determinant) on the one hand, and BCTQ score (outcome variable) on the other hand. This will be performed for the different domains of the BCTQ. This results in a single regression coefficient representing the population average difference in the outcome variable over time that incorporates between-subject and within-subject correlations.

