#### Analysis plan

Descriptive statistics will be provided using mean with standard deviation (SD), median with interquartile range (IQR) or frequencies/percentages depending on the type of distribution of the data. Distribution of data will be assessed using histograms and skewing.

Values of *p* < 0.05 will considered statistically significant. All analysis will be on an intention- to-treat basis. We will correct for multiple testing, *P*-values will be corrected by the Bonferroni method [21].

For exclusion and dropout, numbers and reasons are reported to ensure internal validity. A flow- chart will show the number of patients lost during follow-up including reasons for the loss of follow-up. An analysis on basic characteristics will be performed to control for selection bias. Missing values will be imputed using multiple imputations when meeting the assumption of missing completely at random/missing at random (MCAR/MAR), as imputation will always increase precision and often also reduce bias [22, 23].

Table 1 shows the variables at each study visit.

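### The trial is sized at an unadjusted α of 0.05, but the primary analysis covers two BCTQ domains under Bonferroni, which leaves about 71% power rather than 80%; the power is also mislabelled as β = 0.80

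*Protocol article*

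**What the plan says.** All places are in the protocol article.

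- **Sample size, recruitment and consent.** Two sets of minimal clinically important changes at 3, 6 and 12 months are listed: "0.4, 0.7, and 0.7 points on a 5-point scale for symptom severity score" and "0.3, 0.3, and 0.4 points on a 5-point scale for function status scale". On spread: "The standard deviation used is 0.7, based on a 12 months follow-up after decompression". An unspecified formula for longitudinal continuous outcomes then gives the result: "a total of 144 patients will be needed (α = 0.05, β = 0.80". With 10% dropout this becomes 160. The section does not say which of the six differences was used, and it makes no allowance for multiple testing.
- **Primary outcome.** The change is compared "in BCTQ score between both treatment groups at 3, 6 and 12 and 18 months follow-up".
- **Primary study parameter.** A linear GEE relates treatment group to BCTQ score. "This will be performed for the different domains of the BCTQ". The section adds that the model yields one coefficient, summarising the difference between arms across follow-up.
- **Analysis plan.** The threshold is p < 0.05, followed by "We will correct for multiple testing", using Bonferroni. The statement is general: it neither names the family of tests nor exempts the primary outcome.

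**The concern.** Two statements do not fit together, and one label is wrong.

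First, the size is set at α = 0.05, as if for a single test. The primary analysis produces one test per BCTQ domain, no domain is named as the primary one, and the plan's own multiplicity rule, as written, covers these tests. With two domains, each is judged at 0.025 or stricter. A size that gives 80% power at 0.05 cannot give 80% at 0.025, so the stated power is not the power of the planned analysis.

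Second, "α = 0.05, β = 0.80" labels 0.80 as the type II error.

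At stake are the accuracy of the stated power and the freedom left open at analysis. With neither a primary domain nor a Bonferroni family fixed, both could be chosen after the results are known.

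**Working it through.** **Inputs.** From the sample size section: α = 0.05, the printed 0.80 read as power, SD 0.7, listed differences of 0.3, 0.4 and 0.7, 144 evaluable, 10% dropout. Allocation is 1:1 (allocation section). Assumed because not stated: two-sided testing, T measurements per patient, and within-patient correlation ρ.

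**1. Dropout step.** 144 / 0.9 = 160. Reproduced.

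**2. Where 144 may come from.** For one measurement, n per arm = 2(z₀.₉₇₅ + z₀.₈₀)² SD² / d², with 1.960 + 0.842 = 2.802:

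| d | n per arm | total |
|---|---|---|
| 0.3 | 2 × 7.849 × 0.49 / 0.09 = 85.5, so 86 | 172 |
| 0.4 | 2 × 7.849 × 0.49 / 0.16 = 48.1, so 49 | 98 |
| 0.7 | 2 × 7.849 × 0.49 / 0.49 = 15.7, so 16 | 32 |

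None of these is 144. A repeated-measures formula multiplies n by [1 + (T − 1)ρ] / T, which is at most 1. So 0.4 and 0.7 cannot reach 144 at any ρ up to 1. For 0.3, 72 per arm requires a factor of 72 / 85.47 = 0.842, which gives ρ = 0.76 (T = 3), 0.79 (T = 4) or 0.80 (T = 5). Hence 144 is consistent with d = 0.3 and ρ near 0.8, but it cannot be reproduced uniquely.

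**3. β read literally.** Power of 0.20 uses 1.960 − 0.842 = 1.118. At d = 0.3, 2 × 1.118² × 0.49 / 0.09 = 13.6, so 14 per arm and 28 in total. With T = 4 and ρ = 0.8 the factor is 3.4 / 4 = 0.85: 11.6, so 12 per arm and 24 in total. Neither is near 144, so the 0.80 is the power.

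**4. Power under the multiplicity rule.** Premise: 144 gives 80% at two-sided 0.05, so the standardised effect at the sizing difference is 2.802. Two domains under Bonferroni use 0.05 / 2 = 0.025 each, with critical value z₀.₉₈₇₅ = 2.241.

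Power = Φ(2.802 − 2.241) = Φ(0.560) = **71%**.

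This step needs neither d, SD, T nor ρ. If α = 0.05 were one-sided, the same premise gives Φ(1.645 + 0.842 − 1.960) = Φ(0.526) = 70%.

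**5. Size that restores 80%.** Inflation = (2.241 + 0.842)² / 2.802² = 1.211. 144 × 1.211 = 174.4, so 88 per arm and **176 evaluable**; 176 / 0.9 = 195.6, so 196 enrolled. Equivalently, the difference detectable with 80% power from 144 rises by a factor of 3.083 / 2.802 = 1.10, for example from 0.30 to 0.33.

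**6. By domain, if d = 0.3 was the sizing difference.** The function scale at 0.3 has 71%. The symptom scale at its smallest listed value, 0.4, with the same SD and correlation, has Φ(2.802 × 4/3 − 2.241) = Φ(1.494) = **93%**.

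**7. If both domains had to succeed.** No Bonferroni correction is then needed. At 0.05 each, power is 80% (function, 0.3) and Φ(3.735 − 1.960) = 96% (symptom, 0.4). The joint power is at most 80% and at least 0.80 + 0.96 − 1 = 76%.

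**The case against.** **Time points.** A reader might infer that two domains at four follow-up times make eight primary tests, with a much larger loss. The text does not support this. The primary study parameter section reduces each domain to one coefficient over time, and no section plans a separate primary test at each visit. The primary outcome section lists when the BCTQ is compared; it does not multiply the tests.

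**A missed effect.** A reader might also conclude that a real difference will probably be missed. That goes too far: 71% power is a 29% chance of a miss, and only for the sizing difference. If the symptom scale truly differs by 0.4, the chance that at least one domain is significant is at least 93%.

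**Derivation of 144.** A correlation near 0.8 is one route, not the only one. At d = 0.3, 90% power with T = 4 and ρ = 0.5 gives 2 × 3.242² × (0.49 / 0.09) × 0.625 = 71.5, so 72 per arm; Bonferroni over two domains would then leave Φ(3.242 − 2.241) = 84%. Baseline adjustment at one visit with baseline correlation 0.4 gives 85.5 × (1 − 0.16) = 71.8, also 72 per arm. These routes are possible, but the printed 0.80 makes 80% the natural reading.

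**What an article may leave out.** The correlation, the number of measurements and the exact Bonferroni family may be set out in a fuller document, and their absence here is not the point. What stands is a conflict between statements that the article does make: an unadjusted α for sizing, several primary domains, and a correction with no exemption for them.

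**The β label.** It is a slip, and the calculation of 144 was evidently not affected by it. It is still wrong as printed.

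**Conclusion.** The point holds in a limited form. The label β = 0.80 is an error for power 0.80. The stated 80% is not what the planned primary analysis delivers: with two BCTQ domains under Bonferroni, power at the sizing difference is about 71%, and about 176 evaluable patients would be needed for 80%.

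This rests on three assumptions: that 144 gives 80% at two-sided 0.05, that the domains are the two scales named in the sample size section, and that the Bonferroni statement covers the primary outcome as it literally does. If secondary tests share the same family, the divisor is larger and power is lower; two is the mildest reading that applies the correction to the primary domains. Placing the loss on the function scale further assumes a sizing difference of 0.3, the only listed value that reaches 144 with SD 0.7, two-sided 0.05 and 80% power.

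The loss is moderate, does not extend to every domain, and can be put right before analysis.

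**What to change.** In the sample size section, replace the parenthesis with power 0.80 (β = 0.20), and state the target difference and the BCTQ domain it belongs to. Then choose one of the following before analysis:

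- **(a) One primary criterion at 0.05.** Name one BCTQ domain as primary, or require both domains to succeed and state the power for that joint criterion (76% to 80% under the assumptions in the check). State in the analysis plan that Bonferroni applies only to the secondary family.
- **(b) Two primary domains under Bonferroni.** Keep both at 0.025 and restate the power as about 71% for the sizing difference.

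Under either option, state that the primary family contains one coefficient per domain and no separate tests by visit. The choice of primary domain is the sponsor's; that 0.3 on the function scale is compatible with 144 does not by itself settle it.

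Neither option needs more patients. The cost is wording, plus one of three consequences: one domain loses primary status, both must succeed, or the stated power becomes less favourable. Keeping 80% under (b) would instead require about 176 evaluable and 196 enrolled patients, 36 more than planned.

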### Statistical methods

#### Primary study parameter

Difference in change in BCTQ: Linear generalized estimating equation (GEE) analyses will be used to study the longitudinal relationship between treatment group (determinant) on the one hand, and BCTQ score (outcome variable) on the other hand. This will be performed for the different domains of the BCTQ. This results in a single regression coefficient representing the population average difference in the outcome variable over time that incorporates between-subject and within-subject correlations.

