#### Secondary study parameters

- Difference in change in PRUNE: Linear generalized estimating equation (GEE) analyses will be used to study the longitudinal relationship between treatment group (determinant) on the one hand, and BCTQ score (outcome variable) on the other hand. This will be done for the different domains of the PRUNE.- Difference in PREM vs change in PROM: The PREM score is a continuous outcome and will be analyzed using an independent T-test if distributed normally and a Mann–Whitney U test when not. The change in PROM (BCTQ) score is a continuous outcome and will be analyzed using a paired T- test if distributed normally and a Wilcoxon signed rank test when not. To assess the association between PREM scores and PROM change scores, linear regression analyses will be performed. Multivariable regression models will be used to adjust for potential confounding of various patient and disease characteristics, including age, sex, body mass index, smoking and duration of disease. All domains of the PREM (pre-, intra- and postoperative care and communication) were introduced simultaneously in the same model as independent to determine to what extent the variation in treatment outcome between patients could be explained by the experience with health care, as measured by the PREM. The outcome is measured by the beta-coefficient, showing the change in PROM associated with 1 absolute point increase in PREM subscale.- Sensibility: Sensibility is measured using two-point discrimination, resulting in a categorical outcome. The outcome includes > 2 categories and will be compared using a Chi-Squared test.- RTW, Complications, Scar Aesthetics: Return of full function in days, number of complications and scar aesthetics are continuous outcomes and will be analyzed using an independent T-test.- Correlation between VAS, Bishop, two-point discrimination and both PROMs: The association between VAS score, Bishop score, two-point discrimination and PROMs (both BCTQ and PRUNE) will be determined using the Pearson or Spearman correlation, depending on the data distribution. Analyses will be performed in two dimensions: 1) the correlation between preoperative VAS score, Bishop score, two-point discrimination and both PROMs and 2) the association between change in VAS score, Bishop score, two-point discrimination and both PROMs (12-month score minus preoperative score).

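### The primary GEE is worded as one time-averaged difference in BCTQ level and does not say how the pre-operative score enters, so it does not match the stated difference in change at four visits; the PRUNE model names the wrong outcome

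*Protocol article*

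**What the plan says.** Under Primary outcome, the protocol article sets the target: "The difference in change (Δ, preoperatively and postoperatively) in BCTQ score between both treatment groups at 3, 6 and 12 and 18 months follow-up". This is a change from the pre-operative score, compared between arms at four named times.

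Under Statistical methods, Primary study parameter, the item is introduced as a difference in change. The model described is a linear GEE for "the longitudinal relationship between treatment group (determinant) on the one hand" and, as the other side of the relationship, "BCTQ score (outcome variable) on the other hand. This will be performed for the different domains of the BCTQ". Its product is stated: "This results in a single regression coefficient representing the population average difference in the outcome variable over time". The text mentions no change score, baseline covariate, visit term or arm-by-visit term, and does not say whether the pre-operative score is among the repeated outcomes.

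Under Secondary study parameters, the PRUNE item repeats the same sentence without changing the outcome: "BCTQ score (outcome variable) on the other hand. This will be done for the different domains of the PRUNE".

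**The concern.** With BCTQ score as the dependent variable and treatment group as the named determinant, the coefficient is a difference in level averaged over the rows supplied. The primary outcome is a difference in change at each of four times. The two agree only under conditions that the text does not fix, and one averaged coefficient cannot supply four visit-specific differences.

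What is at stake depends on how the pre-operative score is handled:

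- **Post-operative scores only.** The comparison is valid, but precision available from a score already collected goes unused.
- **Pre-operative score as an outcome row, group-only model.** A true effect is averaged with a row on which the arms do not differ in expectation, so the estimate shrinks towards zero. The trial is labelled non-inferiority, and shrinkage of this kind favours that conclusion. For the superiority hypothesis under Objectives, it costs power.

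Patients, doctors and researchers are unblinded. If the wording stays open, the choice between the two could be made with the data in view.

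For PRUNE, the first-listed secondary outcome, the between-group model as written has no PRUNE outcome.

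**Working it through.** **Inputs from the protocol article (Sample size, recruitment and consent; Allocation and blinding).** SD 0.7; 1:1 allocation; "a total of 144 patients will be needed (α = 0.05, β = 0.80"), read as 80% power; hence 72 evaluable patients per arm. The smallest of the cited minimal clinically important changes is 0.3 points (function scale), used here as the effect.

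**Assumptions, not in the document.** Two-sided test; equal correlation ρ between any two measurements of one patient; a post-operative effect constant over visits; complete data; rb, the correlation of the baseline score with each follow-up score.

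**The plan's own figures.** 144/0.9 = 160 reproduces. The 144 cannot be derived from the stated inputs alone, because the effect used, ρ and the number of measurements are not given. The usual longitudinal formula for T measurements is

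n per arm = 2(1.96 + 0.842)² × SD² × [1 + (T − 1)ρ] / (T × δ²).

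With δ = 0.3 and SD = 0.7, the part without the correlation factor is 85.47. For T = 4 and ρ = 0.79 the factor is (1 + 3 × 0.79)/4 = 0.8425, and 85.47 × 0.8425 = 72.0 per arm. So 144 is attainable. The value ρ = 0.79 used below is back-solved in this way, with ρ = 0.5 as an alternative.

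**Reading A: four post-operative rows, group only.** The expected coefficient is 0.30. Its variance is 2 × 0.49 × (1 + 3ρ)/4 / 72.

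- ρ = 0.79: SE = √(0.98 × 0.8425/72) = 0.1071; 0.30/0.1071 = 2.80; power Φ(2.80 − 1.96) = 80%.
- ρ = 0.5: SE = √(0.98 × 0.625/72) = 0.0922; 0.30/0.0922 = 3.25; power 90%.

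**Reading A with baseline as covariate.** The variance is multiplied by 1 − rb²/[(1 + 3ρ)/4]. At ρ = 0.79:

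| rb | Variance ratio | Reduction | Power |
|---|---|---|---|
| 0.3 | 1 − 0.09/0.8425 = 0.893 | 11% | 84% |
| 0.5 | 1 − 0.25/0.8425 = 0.703 | 30% | 92% |
| 0.7 | 1 − 0.49/0.8425 = 0.418 | 58% | 99% |

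The unadjusted power is 80%.

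**Reading B: pre-operative score plus four post-operative rows, group only.** The expected baseline difference is zero, so with five equally weighted rows the expected coefficient is (0 + 4 × 0.30)/5 = 0.24. Its variance is 2 × 0.49 × (1 + 4ρ)/5 / 72.

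- ρ = 0.79: SE = √(0.98 × 0.832/72) = 0.1064; 0.24/0.1064 = 2.26; power 62%, against 80% under reading A.
- ρ = 0.5: SE = √(0.98 × 0.60/72) = 0.0904; 0.24/0.0904 = 2.66; power 76%, against 90% under reading A.

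**Check by simulation.** 200 replicates of an exchangeable GEE with ρ = 0.5 and a true effect of 0.30 gave mean coefficients of 0.252 (reading B) and 0.315 (reading A). Both lie somewhat above expectation, which I take to be sampling error, so I use only their ratio: 0.252/0.315 = 0.80, the predicted 4/5.

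**PRUNE.** No arithmetic applies. The item's title and its closing reference to domains are about PRUNE, while the dependent variable named between them is BCTQ.

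**The case against.** The article names treatment group as the determinant but never says it is the only one. It condenses a fuller protocol, and visit coding, covariates and the handling of baseline are commonly settled in an analysis plan that is not shown. The item is introduced as a difference in change, so the intention is visible. If the outcome rows are the four visits listed under Primary outcome, randomisation makes the expected difference in level equal to the expected difference in change. Chance baseline imbalance is then already covered by the standard error, so the loss is one of efficiency. The dilution needs a model that no sentence actually describes. The proposed repair also keeps a visit-averaged contrast as primary.

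Most of this stands. A reader might infer that the analysis cannot estimate the primary outcome, or that it is biased towards no difference. The document supports neither as a general statement: the first fails under reading A, and the second holds only under reading B. A reader might also infer that PRUNE is never analysed. That is too strong, because the correlation analyses under Secondary study parameters use PRUNE, both pre-operatively and as change.

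What the objection does not remove is the mismatch in what is stated. The article fixes an outcome variable, a determinant and a single coefficient; these do not match its own primary outcome, and the choice between the two readings is left open. A visit-averaged contrast is a sound primary choice once baseline is handled explicitly and the visit-specific differences are also reported. The PRUNE slip is probably a copying error with a clear intention, but it still needs correcting.

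**Conclusion.** The concern holds as a mismatch between the primary outcome and the primary model, together with a wrong outcome name in the PRUNE between-group model. It does not establish that the primary result will be biased.

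The consequence depends on a choice the article does not state. With post-operative rows only, the estimate is valid, and the cost is the forgone variance reduction of about 11% to 58%. With the pre-operative score as a row in a group-only model, the effect is understated by a fifth and power drops by about 18 percentage points at ρ 0.79, or about 14 at ρ 0.5, with shrinkage in the direction that helps a non-inferiority claim.

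These sizes rest on an effect of 0.30, SD 0.7, 72 per arm and two-sided 0.05, with assumed ρ and rb. The one-fifth shrinkage further assumes five equally weighted, complete rows and a constant post-operative effect. The mismatch itself and the PRUNE error depend on none of these.

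**What to change.** **Primary study parameter.** State that the outcomes are the post-operative BCTQ domain scores at 3, 6, 12 and 18 months, modelled by linear GEE on arm, baseline score of the same domain, visit and arm-by-visit. Name the arm effect averaged over the four visits as the primary contrast, and report the visit-specific contrasts alongside it. State that the pre-operative score is not used as an outcome row in a group-only model. Further baseline covariates, such as McGowan grade, are optional.

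**Secondary study parameters, PRUNE item.** Replace BCTQ score as the outcome variable with the PRUNE domain score, and use the same model.

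**Cost.** Analysis wording only. The pre-operative scores are already needed to compute the stated changes, so no visit, measurement or patient is added. If a fuller analysis plan already contains these terms, the remaining work is to bring the article's wording into line with it.
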